#### Exercise Interventions

##### RT

Subjects will perform 10 resistance exercises for the major muscle groups (Table 4). The training program is lower extremity-focused, with 70% of exercises isolating the lower extremities. For the first 2 weeks subjects will perform 1–2 sets of 15 repetitions for each of the ten exercises, using a weight that elicits a rating of perceived exertion (RPE) at the end of the final repetitions of the respective sets of 5–6 (0–10 scale) as reported by the subject. Rest between sets/exercises will range from 30 to 60 s. Weeks 3–4 subjects will perform 2–3 sets of 12–20 repetitions at an RPE of 5–8 with 60–90 s rest between sets. Weeks 5–8 subjects will perform 3–4 sets of 10–20 repetitions at an RPE of 6–8 with 60–90 s rest between sets. Weeks 9–12 subjects will perform 3–5 sets of 6–20 repetitions at an RPE of 7–8 with 60–90 s rest between sets. Contraction velocity for each exercise will be moderate (180–240°/sec), with duration lasting ~2 s for concentric actions and 2 s for eccentric actions (63). This protocol meets the ACSM resistance training recommendations for older adults (15), and progresses from entry-level to a more demanding protocol. Duration is expected to last ~45–75 min. Subjects will occasionally be asked their perceived effort level on 1–10 scale after individual exercise sets to ensure that they are exercising at the prescribed intensity.

**Table 4 T4:** Resistance training group exercises.

**Daily exercises**	**Rotating exercises**
Leg press Knee extensions Leg curls Calf raises Chest press	Lunges Step-ups (weighted or unweighted) Hip abduction Hip bridge (single- or double-leg) Box squat Sumo squat Planks (knee and elbows or knees and toes) Biceps curls Push-ups (incline or flat) Seated cable pull-down Seated cable row Triceps extensions Shoulder overhead press Lateral arm raises

*The five Daily Exercises are performed during each exercise session. The remaining five exercises each session will be chosen by the exercise supervisor from the list of Rotating Exercises*.

##### MICT

The MICT will be performed on a stationary bicycle (Peloton Interactive, Inc. New York City, NY, USA) interfaced with a computer monitor that plays selected pre-recorded “spin classes.” Heart rate and power output are displayed in real time. The goal of MICT is to maintain an output that elicits the prescribed heart rate throughout the exercise session. Heart rate reserve (HRR) will be calculated by subtracting the subject's resting heart rate (obtained during medical history check at visit 1) from their maximal heart rate (obtained during the GXT). The progression of the 12-week program will go as follows. For the first week subjects will cycle for 20–30 min at 50–60% of their HRR. Week 2 subjects will cycle for 20–30 min at 55–65% of their HRR. Weeks 3–4 subjects will cycle for 30 min at 60–70% of their HRR. Weeks 5–8 subjects will cycle for 30–45 min at 65–75% HRR, and in weeks 9–12 subjects will cycle for 45 min at 70–75% HRR. These ranges are based on recommendations from a meta-analysis describing a dose-response relationship between exercise intensity and VO_2_max adaptations in older adults (64), An exercise supervisor will oversee each exercise session. The target output (in watts) will be determined during the first exercise session by having the subject cycle for 5 min at a cadence of 75 RPMs with a resistance that produces 50 W. Once a consistent heart rate is established (using a chest-strap heart rate monitor), we will increase or decrease the resistance until the target heart rate is maintained. The target output for each subsequent session will be the highest average output from the previous week. If there was no increase from the previous week, target average output will be manually increased by 3%. If the subject is maintaining the target output but not achieving the target heart rate, output will be increased incrementally by 2–5 W until the heart rate is maintained in the target range. During each exercise session the subject will follow the cadence recommendations of the spin class instructor (ranging 50–100 RPMs) while the in-person exercise supervisor modifies the resistance to ensure the output is maintained within the target range. At times the subject may be cycling at the target output but have a heart rate that exceeds the target. In these cases heart rate range takes precedence over output range, and output will be decreased until the target heart rate is maintained. This may occur when cycling at higher cadences (e.g., 90–100 RPMs). At the end of each exercise session subjects will be asked their perceived effort level for the entire session on a 1–10 scale and a Borg 6–20 scale. See Table 5 for exercise duration of each session.

**Table 5 T5:** MICT and HIIT exercise groups cycling duration.

**Session #**	**1**	**2**	**3**	**4**	**5**	**6**	**7**	**8**	**9**	**10**	**11**	**12**
	**Week 1**			**Week 2**			**Week 3**			**Week 4**		
MICT	20	20	30	30	20	30	30	30	30	30	30	30
HIIT	20	20	30	30	20	30	15	15	15	15	15	15
**Session #**	**13**	**14**	**15**	**16**	**17**	**18**	**19**	**29**	**21**	**22**	**23**	**24**
	**Week 1**			**Week 2**			**Week 3**			**Week 4**		
MICT	30	30	30	30	45	30	30	45	30	45	30	45
HIIT	15	20	15	15	20	15	20	15	20	20	15	20
**Session #**	**25**	**26**	**27**	**28**	**29**	**30**	**31**	**32**	**33**	**34**	**35**	**36**
	**Week 1**			**Week 2**			**Week 3**			**Week 4**		
MICT	45	45	45	45	45	45	45	45	45	45	45	45
HIIT	20	20	20	20	30	20	20	30	20	20	30	20

*Duration (in minutes) of cycling for the moderate-intensity continuous training (MICT) and the high-intensity interval training (HIIT) groups for exercise sessions 1–36*.

##### HIIT

Subjects in the HIIT group will use the same stationary bicycle setup as in the MICT group. The progression of the 12-week program will go as follows. Subjects will cycle continuously for 20–30 min at 50–60% of their HRR for the first week, and 20–30 min at 55–65% of HRR for the second week, similar to the MICT group. During the subsequent weeks, subjects will perform bouts of higher intensity cycling (target intensity of 80–100% of their HRR) interspersed with low- intensity rest periods (target intensity of 40–60% of their HRR). Here, the duration of the bout (or interval) will range from as little as 15 s and upwards of 1 min, and rest periods will be matched in a work/rest ratio of 2:1, 1:1, or 1:2 (1:1 on average). During weeks 3–4 the intensity will be at 80–95% of their HRR and the overall duration will last 15–20 min. Weeks 5–8 the intensity will be at 80–100% of their HRR with a duration of 15–30 min. During weeks 9–12 intensity will be at 85–100% of their HRR and duration will last 20–30 min. When the subject begins week three, the target average output will be determined by multiplying the subject's best average output from the first 2 weeks by 1.2. The subject will cycle at the target average output for the first 2–3 min of each session, at 150–300% of their target average output during the high-intensity intervals, and at 25–50% of their target average output during their low-intensity intervals in order to achieve the target heart rate ranges. The target average output for each subsequent week of exercise sessions will be the highest average output from the previous week. If there was no increase from the previous week, target average output will be manually increased by 3%. Subjects will complete 15, 20, or 30-min sessions throughout the study (Table 5) and will begin each session by cycling at the target average output for 2–4 min, followed by several high- and low-intensity intervals. Subjects will cycle at a high intensity for ~6 total min during 15 min sessions, ~8 total min during 20 min sessions, and ~10 total min during 30 min sessions, maintaining an average work/rest ratio of 1:1. The subject will follow the cadence recommendations (ranging 50–100 RPMs) of the spin class instructor while the in-person exercise supervisor modifies the resistance to ensure the output is maintained within the target ranges. It is unlikely that the subject's heart rate will reach 40–60% of HRR during the rest intervals, however, an output that is 25–50% of the target average output should elicit a heart rate that is 40–60% of HRR under normal conditions. Therefore, rest intervals will be long enough that the subject's heart rate will decrease by 5–20 beats per minute prior to the start of the next high-intensity interval. At the end of each exercise session subjects will be asked their perceived effort level for the entire session on a 1–10 scale and a Borg 6–20 scale. See Table 5 for exercise duration of each session.

#### Intervention Discontinuation

Participation in the study will be discontinued if the subject fails to follow the study requirements, experiences serious side effects (e.g., heart attack, exercise related injury), changes the dosage of anti-hypertensive medication or starts taking an exclusionary medication during the course of the study (Table 1), or requests to be removed from the study.

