Resistance exercise appears to have minor effects on cardiovascular disease (CVD) risk factors, though its benefits include the prevention of musculoskeletal injuries, muscle wasting, and impairments in physical function (16). On the other hand, aerobic exercise is effective at reducing CVD risk by improving heart, lung, and metabolic function, though it appears to have little effect on muscular properties (17). However, recent work indicates that the absence of muscular adaptations in response to aerobic training may be related to exercise intensity and mode of exercise (18, 19). The most popular form of physical activity in older adults is walking, and recommendations for older adults promote walking as the primary means to increase physical activity levels (15, 20, 21). While walking may challenge older adults and result in cardiovascular improvements, the relatively low intensity of muscular contractions would be unlikely to elicit hypertrophy or functional adaptations of the leg muscles (22). Even higher intensity running does not seem to result in increased muscle size or strength (19, 23), and running may blunt the muscular benefits of resistance training when performed concurrently (24). In contrast, stationary bicycle training can increase muscular strength and size (25–27), and does not seem to interfere with the muscular adaptations to resistance training (24). Bicycle high-intensity interval training (HIIT) in particular may be the ideal form of aerobic exercise able to elicit muscular adaptations. Young adults performing bicycle HIIT demonstrate improved muscle strength (28) and power (29, 30), along with enhanced cardiorespiratory function (31).

HIIT has gained popularity in recent years, with most research in middle-aged and older cardiac rehabilitation patients (32, 33). Compared to traditional aerobic training, HIIT typically has a greater effect on VO_2_max (9.1% greater increase on average) and other CVD risk factors (e.g., cholesterol, blood pressure) (33). While its success in rehabilitation is encouraging, the effectiveness of HIIT as a general exercise strategy for older adults has not been adequately investigated, with few studies reporting physiological adaptations to HIIT in older adults (33–44). Furthermore, limitations make it difficult to generalize these studies to a healthy aging population. Specifically, these studies have had one or more of the following methodological confounds:

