Inclusion Criteria: •Age 60–75 years with no significant health issues or conditions that, in the investigators' opinion, would limit the subject's ability to complete the study per protocol or that would impact the capability to get an accurate measurement of study endpoints. •Body mass index between 18 and 40 kg/m^2^. •Willingness to maintain current diet and adhere to the intervention programs described for the study and willing to undergo all testing procedures. •Able to read, understand, and complete study-related questionnaires. •Able to read and understand, and willing to sign the informed consent form (ICF). •Six-min walk distance of 450–725 meters for men and 400–675 meters for women.Exclusion Criteria: •Short physical performance batter (SPPB) score <8. •Any activities of daily living disability (difficulty feeding, dressing, continence, bathing, toileting, and transferring). •Lives in a nursing home or assisted living facility. •Known neuromuscular or neurological conditions affecting somatosensory or motor function or control (e.g., hemiplegia, multiple sclerosis, peripheral neuropathy, Parkinson's disease, Myasthenia Gravis, Ataxia, Apraxia, post-polio syndrome, mitochondrial myopathy, etc.). •Unable to communicate because of severe hearing loss or speech disorder. •Severe visual impairment, which would preclude completion of the assessments. •Cancer requiring treatment currently or in the past 2 years (except primary non-melanoma skin cancer or *in situ* cervical cancer). •Hospitalization (medical confinement for 24 h), or immobilization, or major surgical procedure requiring general anesthesia within 12 weeks prior to screening, or any planned surgical procedures during the study period. •Chronic or relapsing/remitting gastrointestinal disorders such as inflammatory bowel disease and irritable bowel syndrome. •Known history of human immunodeficiency virus (HIV) antibody at screening. •Use of systemic glucocorticoids. •Any history of angina pectoris. •Any history of heart failure. •Any history of myocardial infarction. •Any coronary artery bypass graft or percutaneous coronary intervention. •Heart disease that limits exercise (valvular, congenital, ischemic, and hypertrophic cardiomyopathy). •Complex ventricular arrhythmias or heart block. •Chronic obstructive pulmonary disease, cerebrovascular disease, or peripheral vascular disease. •Diabetes mellitus •Severe neuropathy. •Mini-mental state exam score below 19. •Psychiatric conditions that warrant acute or chronic therapeutic intervention (e.g., major depressive disorder, bipolar disorder, panic disorder, schizophrenia) that in the investigators' opinion may interfere with the conduct of study procedures. •Unable to undergo magnetic resonance imaging (MRI) (e. g., body containing any metallic medical devices or equipment, including heart pacemakers, metal prostheses, implants or surgical clips, any prior injury from shrapnel or grinding metal, exposure to metallic dusts, metallic shavings or having tattoos containing metallic dyes). •Unable to reliably undergo exercise or strength tests described for this study. •Participation in progressive resistance exercise 2 or more days/week for most weeks over the 24 weeks prior to screening, OR 150+ min of accumulated aerobic exercise each week for most weeks over the 24 weeks prior to screening. •Current self-reported activity level that, in the investigators' opinion, is considered highly active for older adults. •Participation in any clinical trial within 12 weeks prior to screening. •Limb amputation (except for toes). •Bone fracture within 24 weeks prior to screening. •Any disorder that will not allow completion of the motions required for resistance or aerobic exercise. •Conditions (such as myasthenia gravis, myositis, muscular dystrophy, or myopathy, including drug-induced myopathy) leading to muscle loss, muscle weakness, muscle cramps, or myalgia. •Acute viral or bacterial upper or lower respiratory infection at screening. •Abnormal or uncontrolled blood pressure (BP) at the screening visit defined as BP > 170/100 mmHg. If taking anti-hypertensive medication, have to be on stable doses of medication for more than 3 months. •Current or recent history (within 1 year of screen) of heavy alcohol consumption or drug abuse that in the investigators' opinion may interfere with the conduct of study procedures. •Reports being pregnant, lactating, or that they anticipate becoming pregnant in the next 3-months. If a woman becomes pregnant while on study protocol, they will be withdrawn from the study. Prohibited Medications: Medications that, in the PIs opinion, would confound study integrity by interacting with study outcomes. For instance: •Anti-obesity drugs, nutraceuticals, and dietary supplements that may affect body mass and body composition. •Any drug or supplement known to influence muscle mass or performance including but not limited to anabolic steroids, insulin-like growth factor 1, growth hormone, replacement androgen therapy, anti-androgen therapy.

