### Sample Size

In this proof-of-concept, proof-of-mechanism trial, we report sample size estimates based on previous recommended literature (49). A sample size of ~8 subjects per group will detect a moderate effect. Sample size calculation was based on expected effect sizes for the HIIT cycle, MICT cycle, and RT groups for the primary outcomes of V0_2_max and thigh muscle CSA. Consistent with our “dual benefits hypothesis” we assumed, based on the literature, an 8% increase in thigh CSA for both the HIIT and RT groups (50) and 2% increase for the MICT group (51) and common SD across all groups of 4%. With the assumption of a 2-sided test and alpha level of significance equal to 0.05 an *n* = 7/group yields power of 0.83. With respect to VO_2_max we assumed a 32% increase in the HIIT group, a 15% increase in the MICT group, and a 10% increase in the RT group and common SD across all groups of 14% (52). With the assumption of a 2-sided test and alpha level of significance equal to 0.05 an *n* = 8/group yields power of 0.80. In line with other proof-of-concept, proof-of-mechanism trials, no statistical control for type-I error from multiple comparisons will be considered, and *p*-values will be interpreted with care, as descriptive weights of evidence rather than as confirmatory claims. Lastly, this proof of concept, proof of mechanism trial is needed to test the complex interventions proposed, and the effect sizes calculated from this trial could be used to estimate sample size for a future large-scale clinical trial. Accordingly, we plan to enroll an *n* = 8–10 subjects per group.

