**MUSCULAR TESTING:**							
MVC			X				X
Ballistic			X				X
Twitch force			X				X
VA			X				X
Isokinetic power			X				X
Isokinetic fatigue			X				X
**RANDOMIZATION**			X				

a *Exercise training sessions will be performed three times per week with at least 1 day between sessions, and no more than two exercise sessions on consecutive days in the same week*.

b *Post-intervention functional task testing will be performed immediately prior to the final exercise training session (session 36)*.

c *Baseline testing will be completed within 21 days of Visit 1, with at least 2 days between testing sessions*.

d *Post-intervention testing will be completed within 10 days of the final exercise session, with at least 2 days between testing sessions. 4SST, 4-square step test; DXA, dual-energy X-ray Absorptiometry; GXT, graded exercise test; MMSE, mini-mental state examination; MRI, magnetic resonance imaging; MVC, maximal voluntary contraction; PASE, physical activity scale for the elderly; SEE, self-efficacy for exercise scale; SPPB, short physical performance battery; VA, voluntary activation*.

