## Anticipated Results

### The Dual-Benefits Hypothesis

The HIIT group will see improvements in endurance measures (VO_2_max, 6-min walk distance, isokinetic fatigue) equal to the MICT group and greater than the RT group, and improvements in muscular characteristics (isokinetic power, MVC, thigh muscle volume, VRFD, TRFD, voluntary activation) equal to the RT group and greater than the MICT group.

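### As worded, the discontinuation rule ends study participation rather than exercise alone, so randomised participants who trigger it would apparently have no week-12 outcome

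*Protocol article*

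**What the plan says.** The rule stands in the protocol article under Intervention Discontinuation. The heading speaks of the intervention, but the sentence below it speaks of the study: "Participation in the study will be discontinued if the subject fails to follow the study requirements". A safety trigger applies to anyone who "experiences serious side effects (e.g., heart attack, exercise related injury"). The medication trigger is separate and catches a person who "changes the dosage of anti-hypertensive medication or starts taking an exclusionary medication during the course of the study". The last ground is the person's own wish to leave. No category is given for someone who stops exercising but stays in follow-up.

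The post-tests are tied to the programme. Study Timeline repeats the baseline assessments once the exercise programme is complete. Table 2, footnote b, puts the functional tests immediately before session 36. Footnote d covers the remaining tests: "Post-intervention testing will be completed within 10 days of the final exercise session, with at least 2 days between testing sessions".

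Statistical Methods analyses change from baseline to 12 weeks by one-way ANOVA and Hedges' g, so a participant without a post-test value contributes nothing.

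Two other places bear on the rule. The Exercise Intervention section says that a person who reports a changed medication or dose may not exercise until the study physician has reviewed the change and given clearance. The Adherence section defines success as attending 29 of 36 sessions, without linking this to the discontinuation rule or to an analysis set.

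**The concern.** Randomisation protects the comparison only while the people compared are the people randomised. A rule that removes participants for events occurring during training can undo that protection if the events are related both to the assigned programme and to the outcome.

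Such a link is plausible here. The three programmes differ in intensity and loading, so injury and failure to keep to the programme may differ too. The Introduction says that "HIIT typically has a greater effect on VO_2_max (9.1% greater increase on average) and other CVD risk factors (e.g., cholesterol, blood pressure"), the comparator being traditional aerobic training. Table 1 admits treated hypertensives: "If taking anti-hypertensive medication, have to be on stable doses of medication for more than 3 months". A dose change could therefore be a consequence of training, in which case the rule would remove a responder. Non-compliance might instead remove a poor responder. The direction of any bias is therefore open.

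Two stated uses of the results are exposed. The dual-benefits hypothesis expects HIIT muscle gains "equal to the RT group and greater than the MICT group", and the planned HIIT-RT difference in thigh CSA is zero, so a shift in one arm enters that contrast in full. The Sample Size section adds that "the effect sizes calculated from this trial could be used to estimate sample size for a future large-scale clinical trial". An analysis plan can choose analysis sets and missing-data methods, but it cannot recover tests that were not done.

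**Working it through.** **Does the text lead to missing outcomes?** Three statements combine: the rule ends participation in the study; all post-tests are scheduled from programme completion or the final session; the analysis needs a 12-week value. Nothing in the article provides for week-12 testing after discontinuation. That such people go untested is therefore an inference, but no text points the other way.

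**Is the rule consistent with the rest of the article?** For an anti-hypertensive dose change, the Exercise Intervention section pauses exercise pending physician clearance, while Intervention Discontinuation ends participation. The same event has two different consequences.

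**Planning figure reproduced.** Inputs from Sample Size: VO2max gains of 32, 15 and 10% (HIIT, MICT, RT), SD 14%, two-sided alpha 0.05, 8 per group. With a grand mean of 19, the non-centrality is 8 × (13² + 4² + 9²)/14² = 8 × 266/196 = 10.86. One-way ANOVA on 2 and 21 df then has power 0.789, against the stated 0.80.

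**Illustrative shift.** The number lost (k) and the gap between those lost and completers (d, in SD) are assumptions, because the article gives no dropout rate. All losses are placed in one arm of n.

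Shift in the arm mean = (k/n) × d

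| n | k | d = 0.5 | d = 1 |
|---|---|---|---|
| 8 | 1 | 0.06 SD | 0.125 SD |
| 8 | 2 | 0.125 SD | 0.25 SD |
| 10 | 1 | 0.05 SD | 0.10 SD |
| 10 | 2 | 0.10 SD | 0.20 SD |

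At 8 per arm, 0.0625 to 0.25 SD is 0.9 to 3.5 VO2max points (× 14), against a planned HIIT-MICT difference of 32 − 15 = 17. It is 0.25 to 1.0 CSA points (× 4), against planned differences of 6 (HIIT-MICT) and 0 (HIIT-RT).

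If selection were perfect, so that the lowest (or highest) k of 8 normal values were the ones lost, the expected shift would be 0.20 SD for k = 1 and 0.38 SD for k = 2 (1,000,000 simulated arms).

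**Beside sampling error.** The SE of a difference between two arms of 8 is sqrt(2/8) = 0.5 SD, or 4 × 0.5 = 2.0 CSA points. For VO2max HIIT-MICT, d = 17/14 = 1.21 and the small-sample factor is 1 − 3/(4 × 14 − 1) = 0.945, so g = 1.15 with a 95% half-width of about 1.06. Every illustrated shift is well inside this.

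**Carry-over to a later trial.** A 0.25 SD shift turns d = 1.21 into 0.96 or 1.46. A two-arm t-test with 80% power at two-sided 0.05 then needs 18 or 9 per arm instead of 12.

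**Cost of keeping people in.** Suppose one or two HIIT participants stop early, are tested, and gain half the planned 32%, that is 16%. At 8 per arm the HIIT mean becomes (7 × 32 + 16)/8 = 30 or (6 × 32 + 2 × 16)/8 = 28. Power is from the same ANOVA with the SD held at 14; the last column assumes that removal is unrelated to outcome.

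| Planned n per arm | Participants affected | Retained, half gain | Removed without selection |
|---|---|---|---|
| 8 | 1 | 0.70 | 0.75 |
| 8 | 2 | 0.59 | 0.70 |
| 10 | 1 | 0.83 | 0.86 |
| 10 | 2 | 0.75 | 0.83 |

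**The case against.** The best defence is that the article condenses a fuller protocol. The heading refers to the intervention, and early-termination visits are the sort of detail an article leaves out. This stands in part: a reader might take the text to state that discontinued participants are not tested, and it does not. But the operative sentence names the study, and the post-test timing agrees with that reading.

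Second, the physician review in the Exercise Intervention section softens the rule for many medication changes. That is true for drugs the rule does not name. For anti-hypertensive dose changes it leaves two conflicting instructions.

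Third, arm dependence is not demonstrated. The blood-pressure remark compares HIIT with aerobic training, not with resistance training, and says nothing about dose changes. Nothing links a dose change to quadriceps gain. The non-compliance trigger is undefined and may be narrow, since the separate 29-of-36 definition would have little purpose if low attenders were always removed. All of this stands, so differential removal is a plausible risk and no more.

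Fourth, this is a phase 1B proof-of-mechanism trial with descriptive p-values, and prohibited drugs are excluded because they could interact with the outcomes. Estimating adaptation in those who trained as planned is a legitimate aim. It does not require leaving the others unmeasured, because that analysis remains available when they are tested.

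Finally, testing may be unsafe after a serious event, or declined by someone who leaves. Those losses cannot be recovered. The recoverable cases are mainly non-compliance, medication change and injuries that still permit some tests.

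**Conclusion.** The point holds in a limited form. Followed as written, the rule would apparently leave some randomised participants without a week-12 outcome for reasons arising after randomisation, and it conflicts with the physician-review provision for dose changes. The arm comparison and Hedges' g are therefore open to selection bias.

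Its direction and size cannot be determined from the document. The 0.06 to 0.25 SD range rests on assumed losses of 1 or 2 of 8, all in one arm, and an assumed gap of 0.5 to 1 SD; the upper end is the extreme corner of those assumptions. A reader might infer that the comparison is known to be biased, or biased in favour of HIIT. Neither is supported: no dropout rate is given, the triggers can remove good and poor responders alike, and the shifts are small beside sampling error. The case for change is that bias, unlike sampling error, does not shrink in a larger trial planned on these estimates, and that it can largely be avoided at little cost.

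**What to change.** Reword Intervention Discontinuation so that non-compliance, side effects and medication changes stop or pause the exercise only, in line with the physician review in the Exercise Intervention section. Keep withdrawal of consent as the ground for leaving the study.

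Unless consent is withdrawn, invite every randomised participant to those week-12 assessments that are safe for them: Visit 4 functional tests at about days 80 to 83 and Visits 5 and 6 at days 84 to 94. Time these from randomisation rather than from the last session attended. MRI, for instance, needs no exertion.

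Report the comparison by assigned arm together with the group that attended at least 29 of 36 sessions without a prohibited medication change. The second analysis keeps the mechanism question.

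The cost is a change of wording and up to three already-planned visits for a few people. The by-arm analysis is also somewhat diluted, as the power table shows; reporting the attendance-based group beside it addresses this.
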